##### Flexibility

Flexibility will be assessed using the seat and reach test. The measurement will be obtained with the participant seated on the floor with legs extended. A yardstick is placed on the floor and a tape is placed across it at a right angle to the 15 cm in mark. The participant sits with the yardstick between the legs, with legs extended at right angles to the taped line on the floor. Heels of the feet should touch the edge of the taped line and be about 10–12 cm apart. With the heels positioned on the mark, the participant should bend the trunk to reach as far as possible, holding this position approximately 2 s. The result will be the greatest distance reached with the fingertips in 3 attempts (49).

##### Peripheral muscle strength

Peripheral muscle strength will be assessed using manual handgrip dynamometry with analog hydraulic dynamometer JAMAR^®^, Asimow Engineering^®^, USA. The individual should remain in a seated position, and comfortably holding the dynamometer in the dominant hand, with shoulder in neutral rotation, the elbow flexed at 90°, and the forearm in neutral position. The individual should tighten the equipment with the greatest possible strength, being allowed to move only wrist and finger joints. The highest value of three consecutive attempts interspaced by 1 min will be considered (49).

##### Nutritional status

Nutritional status will be assessed by means of anthropometric measurements (body mass, height and waist circumference) and body composition. The body mass will be measured using a digital scale of the brand Filizola^®^, with a variation of 0.1 kg and a maximum capacity of 150 kg. Participants will be asked to wear light clothes and, at the time of measurement, to remove all belongings that can influence the measurement. Height will be double measured using a stadiometer coupled to the balance, allowing a maximum variation of 0.5 cm between measurements. Participants will be measured in an upright position, without shoes and hair accessories, with parallel feet and ankles joined. The body mass index (BMI) will be calculated by the following formula: BMI = body mass (in kg) divided by squared height (in meters). The waist circumference will be measured by the smallest circumference between the last costal arch and the iliac crest using an inextensible anthropometric tape. To take the measurements, the participant will remain standing, erect, with arms extended along the body and feet together being shirtless or with clothes apart, leaving free the area of the waist. Double measurement will be performed and a difference of up to 1 cm will be accepted, using the mean value between the two measures (50).

Body fat percentage will be measured using a bioelectrical impedance analyzer (Biodynamics^®^ 450, São Paulo, Brazil). The electrodes will be positioned at the prominences of the radius and ulna on the posterior surface of the right wrist and between the tibial malleolus and fibula of the right ankle anterior surface. Participants will be advised to wear light clothes without shoes or socks, to maintain at least 4 h fasting before the exam, to not consume caffeine and alcohol during the previous 24 h before the exam, to not exercise within 8 h before the test, and to empty their bladder 30 min before the exam. Patients will lie in a supine position, with arms relaxed along the body and legs straight and apart. Fat-free mass (FFM) and body fat (BF) will be calculated from impedance (resistance and reactance) and anthropometry (body weight and height) data (51, 52).

#### Fatigability

Fatigability is a relatively new concept that assesses perceived effort after the execution of a standardized task (53, 54). Fatigability will be assessed immediately after a 5-min standardized treadmill walk at a speed of 2.4 km/h (0.67 m/s), without inclination. Participants will rate their perceived effort using the Borg perceived effort scale, which ranges from 6 (no exertion at all) to 20 (maximal exertion), with Borg >10 being considered high fatigability (53).

#### Autonomic modulation

Autonomic modulation will be assessed through 30:15 ratio test and heart rate variability analysis using an electrocardiogram and heart rate monitor (Polar V800^®^, PolarTM Electro, Kempele, Finland). The protocol consists of staying 15 min lying in a supine position, then change this posture to a standing position. After standing, the relationship between heart rates (RR intervals) corresponding to maximum tachycardia (around the 15th beat) and maximum bradycardia (around the 30th beat) will be evaluated (55). The RR intervals obtained during the recording of the electrocardiogram and obtained by the heart rate monitor will be used for the analysis of heart rate variability using specific software (Kubios HRV v. 2.2, University of Kuopio, Kuopio, Finland). The heart rate variability indices that will be analyzed in the frequency domain (FFT method) are very low frequency component (VLF), low frequency component (LF), high frequency component (HF) and sympathovagal index (LF/HF). In the time domain, the indices will be mean normal RR intervals (RRi), standard deviation of normal NN intervals (SDNN), square root of the mean squared successive differences from adjacent RRi (rMSSD), and percentage number of pairs of adjacent RRi differing by more than 50 ms from previous RRi (pNN50). SDNN, rMSSD, and pNN50 are acknowledged to reflect the parasympathetic modulation within short periods. Spectral analysis will be performed by the Fast Fourier transform method, with frequency bands corresponding to low-frequency (LF: 0.04–0.15 Hz), high-frequency (HF: 0.15–0.40 Hz), and total power (TP; meaning LF plus HF). The LF and HF reflect a predominance of combined sympathetic-parasympathetic and isolated parasympathetic modulation, respectively, while LF: HF ratio will be adopted as a marker of sympathovagal balance (56).

#### Cardiac morphology and function

The two-dimensional Doppler echocardiogram will be performed to evaluate cardiac function and morphology. The images will be acquired with Epic Cvx equipment (Philips, Andover, MA, USA). The images will be obtained in the LV standard sections: left parasternal sections in the long and short axes (basal, middle and apical), and apical sections in 3-, 4-, and 2- chambers. Cardiac dimensions will be measured according to international recommendations (57). The ejection fraction (EF) and the final diastolic and systolic volumes of the LV will be determined by the Simpson method. Mitral flow will be obtained in the 4-chamber window and its maximum values will be determined in the rapid filling phase (E) and atrial contraction (A), the E/A ratio, and the deceleration time of the E wave. The pulmonary artery systolic pressure will be evaluated by the systolic pressure gradient between the right ventricle (RV) and the right atrium (AD), obtained through the analysis of the tricuspid insufficiency, added to the estimate of the AD pressure (58). The function of the RV will be evaluated at the apical 4-chamber cut. The maximum velocity of myocardial displacement during systole (S’VD) and displacement of the tricuspid ring by the M-mode to the 4-chamber apical cut will be measured. Tissue Doppler will be obtained in the mitral ring in its septal and lateral segments. The maximum velocity of myocardial displacement during systole, at the beginning and end of diastole will be determined. The value of each of these components will be the mean of the respective septal and lateral values.

#### Low back pain

The presence of low back pain in the previous year will be evaluated by the question: “In the past year, did you have pain in your low back?” with the answer options “Yes,” “No,” and “I don’t know.” Among those who answer “Yes” for the previous question, the intensity (0–10 scale, 0 = no pain, 10 = extremely intense pain) and duration [longest consecutive time period (weeks)] of low back pain will be evaluated (59). The Brazilian version of the Roland Morris functionality questionnaire, which includes 24 items (yes or no) on physical disability caused by back pain, will also be applied. The sum of the answers generates a score ranging from 0 (no disability) to 24 (severe disability) (60).

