### Outcomes

Participants will be assessed at baseline, and after three and 6 months of follow-up for all variables, except for echocardiogram exam and fasting blood tests that will be performed at baseline and after 6 months of follow-up. Two clinic visits within a 4-week period for each time point will be performed. The first clinic visit will consist of a clinical interview and physical examination, echocardiogram exam, fatigability evaluation, and cardiopulmonary exercise test. The second clinic visit will include fasting blood tests, nutritional interview, physical fitness evaluation, autonomic modulation assessment, and questionnaires to evaluate back pain, QoL, depression and anxiety, and sleep quality.

The primary outcome will be QoL. Secondary outcomes will include blood pressure, physical fitness components, nutritional status, fatigability, autonomic function, cardiac morphology and function, low back pain, depression and anxiety, stress, sleep quality, medication use and adherence, and biochemical, inflammatory, and cardiac biomarkers.

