#### Medication use, adherence, and adverse drug events

Information on quantity and dosage of the medications regularly used will be obtained from patient’s medical records using the closest medical appointment to the study assessment. Medication adherence will be assessed using the Brazilian version of Medication Adherence Rating Scale (MARS). This questionnaire comprised 10 dichotomous questions (yes/no) to assess intentional (“I avoid using it if I can”) and non-intentional medication adherence (“I forget to use it”). The answers are scored as zero (non-adherence) or one (adherence) and a global score is obtained by summing the items values, so that the result ranges from 0 (low probability of adherence) to 10 (high probability of adherence) (65, 66). The incidence, cause, and intensity of adverse drug events (ADEs) will be determined during the study follow-up based on the information contained in medical records. The Naranjo algorithm and intensity classification will be applied to determine the cause and intensity of ADEs (67).

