### Statistical analysis

A dataset will be prepared including the information from all patients using the Redcap platform. Statistical analysis will be performed using Stata statistical software (version 13.0). The data analysis will comprise the estimation of the mean (standard deviations) for continuous and absolute frequency (percentages) for categorical variables. The effect of the home-based exercise program on the continuous variables over the intervention period will be determined using a linear mixed model. For categorical variables, generalized estimated equations with log link and binomial distribution will be performed to evaluate changes in the proportion of individuals between groups over the time. All measures performed in the intervention and control group will be used, regardless of losses to follow-up or compliance to the protocol during the intervention period, characterizing an intention-to-treat analysis. The variable of interest will be the interaction between time × treatment, which estimates the change rate of the outcome over time. Protocol analysis including only completers will also be performed. Adjustments for baseline prognostic variables will be made in case of unbalance distributions between the groups. A *p*-value < 0.05 will be considered significant for all statistical tests.

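### The yes/no low back pain item, and the longest-spell item that depends on it, look back 12 months at the 3- and 6-month visits, so 75% and 50% of the follow-up windows precede randomisation and the effect on these items is diluted

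*Protocol article*

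**What the plan says.** The Outcomes section of the protocol article names low back pain among the secondary outcomes ("cardiac morphology and function, low back pain, depression and anxiety, stress, sleep quality"). It sets the schedule as "Participants will be assessed at baseline, and after three and 6 months of follow-up for all variables", and exempts only the echocardiogram and the fasting blood tests.

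The Low back pain section says "The presence of low back pain in the previous year will be evaluated by the question" and then gives that item word for word: "In the past year, did you have pain in your low back", with the answers Yes, No and I don't know. Those who answer Yes are also asked for intensity on a 0–10 scale, and "duration [longest consecutive time period (weeks)] of low back pain will be evaluated". No shorter window is given for follow-up visits. A second instrument, scored 0–24 and with no past-year window stated, is planned as well: "The Brazilian version of the Roland Morris functionality questionnaire, which includes 24 items (yes or no) on physical disability caused by back pain, will also".

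The Statistical analysis section takes the time-by-treatment interaction as the effect of interest. Its model for outcomes such as the yes/no item reads: "generalized estimated equations with log link and binomial distribution will be performed to evaluate changes in the proportion of individuals between groups over the time".

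**The concern.** A recall window should fit inside the period in which the intervention can act. Here a 12-month window is reused after 3 and 6 months of follow-up, so most or half of what it records happened before anyone was randomised. Pain in that part is the same in expectation in both arms, and exercise cannot undo it.

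The presence item can change only among participants who had no pain in the pre-randomisation part of the window. The longest-spell item is a maximum over the window, so it cannot fall below the longest earlier spell still inside it. A real benefit would show up as a much weaker interaction and could be reported as no effect on back pain. An analysis plan cannot repair this afterwards, because the question never collects the shorter window. The Stress section shows the contrast: that scale looks back one month, which fits a 3-month visit schedule.

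**Working it through.** **The plan's own figure.** The documents give no figure for back pain. The only stated size is 80 participants, based on the WHOQOL-Bref physical domain (difference 2.2, SDs 2.1 and 3.2, α = 0.05 taken as two-sided, power 0.90). It reproduces: the pooled SD is √((2.1² + 3.2²)/2) = 2.706, which gives 32 per arm, and 32/0.8 = 40 per arm. The 32 expected completers per arm are used below.

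**Share of the window before randomisation.** The formula is (12 − months of follow-up)/12, with inputs from Low back pain (12 months) and Outcomes (3 and 6 months).
- Month 3: (12 − 3)/12 = 75%.
- Month 6: (12 − 6)/12 = 50%.

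These shares need no assumption. Spreading each assessment over two visits within 4 weeks shifts them only slightly.

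**Illustration of the dilution.** Assumed, not in the documents: 40% risk of any low back pain per half-year without exercise, 20% with it, and independent periods.

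| | Control | Exercise | Risk ratio | Difference |
|---|---|---|---|---|
| Months 0–6 only | 40% | 20% | 0.50 | 20 points |
| Past year, asked at month 6 | 1 − 0.6² = 64% | 1 − 0.6 × 0.8 = 52% | 0.81 | 12 points |
| Months 0–3 only | 1 − √0.6 = 22.5% | 1 − √0.8 = 10.6% | 0.47 | 12.0 points |
| Past year, asked at month 3 | 64% | 1 − (√0.6)³ × √0.8 = 58.4% | 0.91 | 5.6 points |

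The arms are expected to be equal at baseline, so under the planned log link the interaction estimates these same ratios.

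**Range under other assumptions.** A second model uses a constant monthly onset rate, halved after randomisation, with 12-month control prevalence of 30%, 50% or 70%.
- Recall since randomisation: ratio 0.51–0.54 at month 3 and 0.52–0.57 at month 6.
- Past-year recall: ratio 0.89–0.93 at month 3 and 0.78–0.85 at month 6.
- Share of the risk difference retained: 41–77% at month 3 and 55–84% at month 6.
- At 50% prevalence and month 6, the difference falls from 13.4 to 9.5 points, and power with 32 per arm from 25% to 11%.

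**If pain recurs in the same people.** Assume that 50% had pain in the pre-randomisation part, that follow-up risk is 50% against 25%, and that a share q of follow-up cases also had pain in the earlier part. Past-year prevalence is then 0.5 + follow-up risk × (1 − q), so the difference is 25 × (1 − q) points.
- q = 0.5: 75% against 62.5%, a difference of 12.5 points.
- q = 0.9: 55% against 52.5%, a difference of 2.5 points.

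Power with 32 per arm falls from 54% to 19% and 4% respectively.

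**The case against.** Four points on the other side deserve weight.

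**Roland Morris is also collected.** It is a 0–24 disability score with no stated past-year window, and it suits the planned mixed model. A reader might infer that the whole back-pain outcome is compromised, but the documents do not support that. The fault lies in the presence and longest-spell items.

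**Intensity has no stated recall period.** A reader might infer that intensity too is fixed by pre-trial pain. The text does not say so. The scale includes 0 for no pain, which fits current intensity at least as well as intensity over the year. Intensity is affected only if it refers to the same year. Duration is not wholly fixed either: a new, longer spell would raise it.

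**The size is assumed, and the scale matters.** Prevalence, the halving and independence are all assumptions. Most of the effect disappears on the ratio scale, but the month-6 illustration keeps 12 of 20 points on the difference scale. The item also has low power even with better recall (25% in the 50%-prevalence case). Both remarks stand. The planned log-link model does, however, work on the ratio scale.

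**Selection among Yes responders.** Comparing intensity or duration only among those who answer Yes at follow-up conditions on a post-randomisation answer. While pre-trial pain largely decides who says Yes, that selection is limited. It would grow once the window is shortened, so the scoring of No belongs with the fix.

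A reader might also suspect the medication data, taken "using the closest medical appointment to the study assessment". That is a records source, not a recall window. The documents give no appointment intervals, so nothing shows that such records would precede randomisation, and the point is not made here.

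**Conclusion.** The point holds for the yes/no item and the longest-spell item. The 75% and 50% shares follow directly from the protocol's wording and schedule, and the direction of bias, towards no effect, follows from them if participants recall accurately. The size does not come from the documents. Under the stated assumptions a true ratio of about 0.5 appears as about 0.8 at month 6 and 0.9 at month 3, and recurrent pain makes the loss larger.

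The consequence is bounded. It concerns part of one of many secondary outcomes, leaves the primary outcome and the sample size untouched, and does not by itself create a false positive. The change is still worth making, because a listed outcome is predictably blunted and the remedy is cheap.

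**What to change.** At baseline, month 3 and month 6, ask presence, intensity and longest spell over one common window of at most 3 months, so that no follow-up window reaches back before randomisation and change is like for like. Keep the one-year question at baseline only, as a descriptor. Score intensity and duration as 0 for a No, so that everyone with a yes or no answer is analysed. Leave Roland Morris as it is.

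The cost is the wording of one questionnaire block and a small departure from the published one-year item. The gain should not be oversold. In the 40% illustration, a 3-month window at month 6 gives 22.5% against 10.6%. That restores the ratio (0.47 instead of 0.81), but the difference stays at about 12 points. Power with 32 per arm rises only from 16% to 25%.

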### Participants and recruitment

Patients with indeterminate form of CD, both sexes, will be consecutively invited by their assistant physicians to participate in the study. If they agree to participate, informed consent will be obtained, and visits will be scheduled in order to explain the procedures related to the research, and perform the evaluations of the variables that will be investigated in the study.

The inclusion criteria are: (1) serological positivity for CD by at least two different methods (ELISA, indirect immunofluorescence, immunochromatography, or chemiluminescence); and (2) having indeterminate CD defined by the absence of symptoms and/or signs of cardiac CD (normal or presence of non-specific CD abnormalities in ECG) and/or digestive CD. Clinical signs of cardiac CD will be assessed by ECG and echocardiographic (ECHO) evaluation. The ECG abnormalities compatible with cardiac CD are 2nd- and 3rd-degree right bundle-branch block, associated or not to left anterior fascicular block, frequent ventricular premature beats (VPBs > 1 by ECG), polymorphous or repetitive non-sustained ventricular tachycardia, 2nd- and 3rd-degree atrioventricular block, sinus bradycardia with heart rate less than 50 bpm, sinus node dysfunction, 2nd- and 3rd-degree left bundle-branch block, atrial fibrillation, electrical inactive area, or primary ST-T wave changes. ECHO abnormalities related to cardiac CD depends on the stage of the disease and may present as segmental left ventricular (LV) wall motion abnormalities (hypokinesia, dyskinesia, akinesia, small, or large aneurysms), LV dilatation, or global LV systolic dysfunction with diffuse hypokinesia (8). In terms of digestive presentation, patients without symptoms compatible with megacolon or megaesophagus will be considered without digestive CD and will not undergo contrasted examinations of the esophagus and colon.

The exclusion criteria are: (1) <18 years old; (2) evidence of non-CD cardiomyopathy; (3) musculoskeletal or cognitive limitations precluding physical exercise; (4) clinical contraindication for regular exercise; (5) regular physical exercise (1 × per week) in the previous 2 months; and (6) pregnancy.

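### Low back pain intensity and duration are recorded only for participants who answer Yes at each visit, so as written these two secondary outcomes are compared in a group formed after randomisation

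*Protocol article*

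**What the plan says.** All references are to the protocol article.

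- **Low back pain.** A gate question comes first: "The presence of low back pain in the previous year will be evaluated by the question", with the answers Yes, No and I don't know. For those who say Yes, two further items are evaluated: "for the previous question, the intensity (0–10 scale, 0 = no pain, 10 = extremely intense pain", and the longest consecutive period of pain in weeks. The Roland Morris questionnaire, "which includes 24 items (yes or no) on physical disability caused by back pain, will also be applied", carries no stated restriction to Yes-responders.
- **Outcomes.** Low back pain is a listed secondary outcome. Everything except the echocardiogram and fasting bloods is assessed at baseline, 3 months and 6 months, so the gate question is put twice after randomisation.
- **Participants and recruitment.** No inclusion or exclusion criterion requires back pain.
- **Statistical analysis.** Continuous outcomes go into a linear mixed model, with the time-by-treatment interaction as the term of interest. "All measures performed in the intervention and control group will be used", whatever the losses or compliance, and this is called intention-to-treat.

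The article gives no value for intensity or duration after a No or an I don't know.

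**The concern.** A participant who answers No at follow-up has no intensity and no duration recorded, although 0 on the intensity scale means no pain. If only recorded values enter the model, the two arms are compared among people who reported pain at that visit. Membership of that group is itself a result of the trial, because exercise may affect who develops back pain.

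Randomisation then no longer protects the comparison. If exercise prevents mild new pain, the control arm's Yes group gains mild cases that the exercise arm's does not. The control mean falls, and a benefit can look like no effect or like harm. That does not fit the intention-to-treat label.

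**Working it through.** **1. Passages side by side.** The Low back pain section limits collection of the two items to Yes-responders. The Outcomes section repeats that collection after randomisation. The Statistical analysis section uses the measures that were performed. For a No there is no measure of intensity or duration. Read together, the three sections give a comparison among post-randomisation Yes-responders.

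**2. Who can enter or leave the group.** The question covers 12 months.

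- At 3 months it still reaches back 12 − 3 = 9 months before baseline; at 6 months, 12 − 6 = 6 months before baseline.
- Anyone with pain at randomisation, or in the 6 months before it, should still answer Yes at both visits, however well exercise works.
- A baseline Yes can become No only if the pain ended earlier than that and has not returned.
- A baseline No becomes Yes if pain arises after randomisation, whatever the recall length. This is the main route by which treatment can change the group.

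**3. Illustration of the new-onset route.** The article gives no pain prevalence or incidence, so every input here is assumed: half of each arm has lasting pain of intensity 6, unaffected by treatment; new pain of intensity 3 arises in 20% of pain-free controls and 5% of pain-free exercisers.

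| | Control | Exercise |
|---|---|---|
| Share answering Yes | 0.5 + 0.5 × 0.20 = 0.600 | 0.5 + 0.5 × 0.05 = 0.525 |
| Mean over everyone, No = 0 | 0.5 × 6 + 0.100 × 3 = 3.300 | 0.5 × 6 + 0.025 × 3 = 3.075 |
| Mean among Yes only | 3.300 / 0.600 = 5.50 | 3.075 / 0.525 = 5.86 |

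Exercise minus control is 3.075 − 3.300 = −0.225 over everyone (a benefit) and 5.86 − 5.50 = +0.36 among Yes-responders (an apparent harm). The sign reverses.

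**4. Scale against the trial's size.** The plan has no figure for this outcome. Its own sample size does reproduce. With pooled SD √((2.1² + 3.2²)/2) = 2.71, difference 2.2, two-sided α 0.05 and power 0.90, n is 32 per group; 32/(1 − 0.20) = 40. With 40 per group, the illustration has 0.600 × 40 = 24 and 0.525 × 40 = 21 Yes-responders. With an assumed SD of 2, the standard error of the difference in means is √(4/24 + 4/21) = 0.60, larger than the 0.36 shift. New cases number 0.100 × 40 = 4 in the control arm and 0.025 × 40 = 1 in the exercise arm.

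**5. The planned model.** The 0.36 is a raw follow-up contrast. The planned term is the time-by-treatment interaction, and new cases have no baseline intensity, so they add little to within-person change. Simulating the same scenario with a random-intercept model (baseline and one follow-up, total SD about 2) gave an interaction of about 0.12 to 0.14 in the adverse direction, with standard error 0.45 to 0.62 at trial size. The figure depends on the assumed within-person correlation and is larger when that correlation is weak.

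**The case against.** **The coding of No may be settled elsewhere.** The article does not say that the model treats No as missing. Scoring it 0 would fit the scale's anchor, and a coding rule could sit in an analysis plan that is not shown. This is the strongest point on the other side. It stands in part: the subset comparison follows from the text as written but is not declared. What remains is that the article fixes a collection rule, not just an open analysis detail, and a later zero would add to that rule.

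**Exercise clearing mild pain.** A reader might infer that exercise turns mild cases into No and leaves the worse ones behind. Past-year recall largely closes that route, as step 2 shows. An illustration in which the mildest 10% to 30% of cases switch to No gives apparent harms of 0.38 to about 0.96 points, but it assumes switching that the question mostly prevents. It should not be used to size the problem.

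**The new-onset example is favourable to the concern.** It assumes a 75% relative reduction (20% to 5%), only mild new cases and no effect on existing pain. That is fair: it shows that the sign can reverse, not that it will.

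**Other back pain outcomes cover everyone.** The presence of pain is asked of all, and Roland Morris as worded is unrestricted. This stands and limits the point to intensity and duration.

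**Medication adherence.** A reader might extend the argument to MARS and say that adherence exists only for those on medicines. The text does not support this: "Medication adherence will be assessed using the Brazilian version of Medication Adherence Rating Scale (MARS", with no restriction to users. Nor can a lack of medicines be read from the inclusion criterion "having indeterminate CD defined by the absence of symptoms", which goes on to specify cardiac or digestive Chagas disease; other conditions and their treatment are not ruled out. At most, the article could state how people taking no medicine are handled.

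**Conclusion.** The point holds for low back pain intensity and duration only. Followed as written, the plan compares these two secondary outcomes among Yes-responders defined after randomisation, which does not match its intention-to-treat description. Pain arising after randomisation can make that group differ between arms and can distort or reverse the comparison.

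The size of the bias cannot be derived from the article. The reversal from −0.225 to +0.36 rests wholly on assumed prevalence, incidence and intensity. In the planned model the same scenario gives a smaller distortion, well within sampling error at 40 per group. It is probably small, but its direction is unhelpful and avoiding it costs almost nothing.

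It would be wrong to infer a threat to the trial's main conclusion: the quality-of-life outcome and the sample size of 80 are not touched. No error is shown for medication adherence. The change should be made, as a secondary-outcome matter.

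**What to change.** - In the Low back pain section, state that a No answer is entered as intensity 0 and duration 0 weeks, and that I don't know is treated as missing.
- State that intensity and duration are compared over all randomised participants at each visit.
- State that Roland Morris is given to everyone, as the text already implies.
- Show the proportion answering Yes by arm and visit beside the mean scores, so that readers can tell fewer people in pain from less intense pain.
- Optionally, add one sentence on how MARS is handled for participants taking no regular medicine. This is a clarification, not a correction.

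The cost is a few sentences and a coding rule, set before the follow-up data are seen. No visit, procedure or participant is added. The downside is a score with many zeros, which fits a normal-error model less well and averages people with and without pain.
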